**8.1.5. Spot Excision and Identification**

Proteins of interest (determined by change from baseline) will be excised robotically using the Ettan Spot-picker (GE Healthcare) and identified by tandem mass spectrometry (MS/MS) on an HPLC-Chip ESI-Trap XCT tandem mass spectrometer or LTQ-FT mass spectrometer. Protein identification will be verified with the use of western blots using specific antibodies.

**8.2 Assessment of Mitochondrial Function (myocardial & lymphocyte)**

Ischemia-reperfusion injury diminishes: mito complex I and IV activities, limits maximal O2 consumption capacity and the efficiency of mito O2 consumption, including greater propensity for the loss of mitochondrial membrane potential (36). Thus the strategy to assess evidence for cardioprotection induced by IPC protocol will be to measure the integrity of mitochondrial respiratory chain enzymes; their activity rates as well as the activation of upstream signalling protein kinases. As our laboratory has long experience in miniaturised metabolic assays for very small clinical samples of tissue and blood (with aid of highly sensitive Cary 300 and Nanodrop spectrophotometers) a number of concurrent assays are permissible in each sample.

**8.2 .1. Mitochondrial Isolation & Preparation**

Mitochondria are isolated from resected myocardial tissue using our custom protocols that permit viable yields from myocardium weighing 5mg or more. In addition, lymphocytes are isolated from whole blood (5ml) by Ficoll-Paque density centrifugation which yields approximately 3-10x106cells/ml. While some lymphocytes are set aside for IPC signalling protein assessments, for mitochondrial respirometric experiments, lymphocytes are permeabilised with digitonin (100 g/mL) for 5 min in the presence of protease inhibitor mixture (Roche) 1mM 4-(2-aminoethyl)-benzenesulphonyl-fluoride hydrochloride (Roche) and 2mM diisopropyl fluorophosphate (Fluka), in a buffer of 250ml sucrose, 10mM HEPES pH7.4 and 1mM EDTA and then digitonin is washed out via centrifugation (1000xg, 4ºC, 5 min, twice).

**8.2.2. Mitochondrial Oxygen Consumption**

As per previous studies (37-39), State III and IV substrate-coupled mitochondrial O2 consumption is measured via a miniature Clarke-type O2 electrode and closed-volume 30L glass chamber (37ºC) in pyruvate/malate buffer (2.5mM/0.5mM), driven by 0.5mM ADP. Maximal O2 consumption rate is determined with the proton gradient uncoupler, FCCP (2M). Complex I-specific O2 consumption is determined with the inhibitor, rotenone (5M), for complex III, antinomycin A (4M). Non-mitochondrial sources of O2 consumption are assessed after the addition of 5mM sodium cyanide (complex IV inhibitor). Stoichiometric estimate of ADP:O consumption is used as an index of efficiency of mitochondrial oxygen use.

**8.2.3. Respiration Enzyme Activities**

In vitro activities for complexes I (NADH dehydrogenase), II (succinate dehydrogenase), III cytochrome bc oxidoreductase, IV (cytochrome c oxidase), are assessed on a Cary 300 spectrophotometer equipped with magnetic stirring and thermostatic control. Activities are normalised to total protein levels and the mitochondrial enzyme, citrate synthase. Complex I, II, III & IV assays are performed via spectrophotometry at 340nm (=6.81mM-1cm-1); 600nm (=19.1mM-1cm-1); 550nm (=19mM-1cm-1); 550nm (=19mM-1cm-1), respectively. Citrate synthase is measured spectrophotometrically at 412nm for 2mins during its conversion of Acetyl CoA + Oxaloacetate to citrate and CoASH, and compared to standards at 0, 2, 4, 6, 8 and 10 U/ml (Sigma).

**8.2.4. MPTP**

Mitochondrial membrane permeability transition pore (MPTP) opening in vitro precedes the collapse of the proton-motive force, disruption of ionic homeostasis and membrane potential, mitochondrial swelling, and rapid ATP hydrolysis that, when occurring irreversibly, accompanies signalling for apoptotic cell death. The feature of mitochondrial swelling coupled to MPTP open-closed transitions is a useful marker for invitro assessment for propensity for MPTP pore opening which occurs with the dissipation of mitochondrial membrane potential, Δ. Mitochondrial membrane potential is estimated by following safranin O (5μM) calibrated fluorescence at an excitation wavelength of 495nm and emission wavelength of 586nm, using 5nm slits, on a Perkin Elmer spectrofluorometer(40). In separate experiments calcium-sensitised molecular-triggered volume changes (mitochondrial swelling) of isolated mitochondria (myocardium) or permeabilised lymphocytes that are linked to MPTP opening are measured via spectrophotometric absorbance changes at 540 nm in 30l. In these studies, the propensity for MPTP opening and the rate of onset will be assessed either in myocardial mitochondria or lymphocyte preparations will be assessed from sham control or RIPC pretreated patient groups. In addition we will investigate the dose-dependant effects of key cytokines such as IL-1, IL-6, TNF and IL-10 on MPTP opening or blockade of RIPC protective effects.

**8.2.5. Western Blot Analysis of Protein Expression, Phosphorylation, and Translocation**

As IPC has been demonstrated to involve activation of a number of protein kinases involved in cardioprotective signal transduction (40-42), the phosphorylation of the PI3Kinase-dependent proteins Akt at Ser473, GSK-3beta at Ser9 and STAT3 at Tyr705 is assessed in myocardial or lymphocyte samples via SDS-polyacrylamide gel electrophoresis protein blotting with respective monoclonal antibodies (R&D Systems, Santa Cruz Biotechnology, Chemicon and Promega). Extracted protein content is examined via SDS-PAGE (electrophoresis/immunoblot) whereby equal quantities of protein (25 μg) from total or sub-cellular fractions isolated via differential centrifugation (cytosolic, mitochondrial, sarcolemmal membrane) are loaded into gel lanes. Component proteins resolved by SDS-PAGE are then transferred electrophoretically to nitrocellulose membranes. Membranes are blocked, washed and probed with primary antibodies for selected proteins (total and phosphorylated). Washed membranes are incubated with secondary antibody, and immunoreactive bands measure densitometrically on a UVP EC3 ChemiHR410 chemiluminescence imaging system.

**8.2.6. Leukocyte Apoptosis**

Apoptosis is assessed using a combination of propidium iodide and annexin V-FITC (R&D systems, MP) fluorescence staining with quantification by flow cytometry as previously described (43).

**8.2.7. Electron Microscopy**

Heart muscle cut into small cubes (~2mm) or cells attached to slides in calcium-free buffer are initially fixed with 4% paraformaldehyde + 0.05% glutaraldehyde. Sections are incubated with antibodies of interest [i.e. Connexin 43, (localizes to mitochondria in preconditioning) in alternate sections], then with gold-conjugated secondary antibodies (R&D Antibodies), fixed with 2% glutaraldehyde, postfixed with OsO4, dehydrated, and embedded into Epon. Ultrathin sections are viewed with a JEOL electron microscope. In addition to immunogold localization of antibodies, mitochondrial and cellular membranes are screened for integrity or injury.

# ADVERSE EVENT REPORTING

- 1. **Definitions**

Adverse event related to the remote preconditioning stimulus will be reported. A potential local effect is significant vascular compromise of the preconditioned limb although this has not been observed in any of the humans studied to date in current studies (HREC#26091C) or previously published studies. Whether or not an event is a serious adverse event (SAE) is at the discretion of the clinical investigator. For this clinical trial, the following will be considered as severe adverse events and will be reported to the Human Research and Ethics Committee if they occur within 30 days of surgery:

1. Death,

2. Stroke,

3. Permanent disablement,

4. Mechanical support

5. Unplanned re-admission

- 1. **Assessment and Documentation of Adverse Events**

Subjects are closely monitored by responsible theatre staff for well being in the perioperative and post-operative period as by standard medical care. Limb perfusion is monitored daily by the nursing staff in the postoperative period in intensive care. Patients will be followed for the period of their intensive care admission which is typically at least 5 days.

SAE data if occurring, will be collected from medical notes for patients cared for at the Royal Children’s Hospital and by telephone interview of the referring doctors for interstate patients if they have returned to the referring centre prior to 30 days post-surgery.

On each SAE, the following will be reported, as per the RCH reporting form (see Appendix): Date of occurrence; Event details (synopsis); Event management (synopsis); Event outcome (synopsis); Is it:        Expected or Unexpected; Is it:        Unrelated, Possibly related, Probably related or Definitely related.

- 1. **Serious Adverse Event Reporting**

SAE Report Forms (See Appendix) will be forwarded without delay (within 24 hours) to the clinical Principal Investigators ([name] or [name]), and to the Chair of the RCH Human Research Ethics Committee within 72 hours.

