# SUBJECT ENROLLMENT AND RANDOMISATION

- 1. **Recruitment**

Patients will be recruited by either the surgeon ([name]) or cardiologist ([name]) at the preadmission clinic or on the ward prior to surgery. The clinician ([name]/[name]) will explain to the patient’s parents/guardians, the research project, their child’s role, and outcomes and will obtain signed consent if granted.

- 1. **Eligibility Criteria**
     1. **Inclusion Criteria**

Patients with tetralogy of Fallot aged one month and older (to 18 years) having surgery for the first time.

- - 1. **Exclusion Criteria**

Patients with chromosomal defects, associated congenital lung malformations and haematological disorders will be excluded.

- 1. **Randomisation Procedures**

Random allocation is made in blocks in order to keep the sizes of the 2 treatment groups similar. In order to avoid predictability, the block size that is randomly selected is 2, 4 or 5, as the sample size must be divisible by the block size. Due to the expected relative uniformity of condition in the patient group and the small number of subjects the design will not be stratified. The randomisation will be performed in secret by a member from Heart Research (not involved in working for the trial) using SPSS statistical software generated randomisation and will place each designation sequentially in numbered envelopes 1 to 40, for patient 1 to 40 and the envelopes will be signed and sealed. The implementer of the RIPC or Sham co ntrol treatment protocols will open one envelope in numerical order immediately prior to placement of the blood pressure cuff and they will apply the RIPC treatment or sham control protocol accordingly.

- 1. **Blinding Arrangements**

[name] will not be blinded as she will be applying the RIPC treatment. She will also be involved in randomisation, sample collection, data collection, data entry and laboratory analysis. Surgeons, perfusionists, anaesthetists will be blinded. Samples will be de-identified and therefore, research laboratory staff will be blinded to the patient’s identity. The blood pressure cuff will be positioned on the thigh for both sham control and RIPC groups, however if other theatre staff witness whether the RIPC treatment protocol is invoked they will not be blinded. As these theatre staff are strictly performing standard clinical tasks and procedures and are not involved in the trial and analysis *per se*, this should not impact the blinding.

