**16. APPENDIX**

# SINGLE SERIOUS Adverse Event (SAE) REPORT FORM

- **All** Internal* SAEs (occurring to RCH participants) **must be reported to the RCH HREC within 24-72 hours of occurrence and must be accompanied by a detailed report of the event.**
- External SAEs (occurring to participants from other sites) **must be reported in a prompt manner if the information impacts the continued ethical acceptability of the trial or requires documentation to be updated (i.e. protocol or PIS).**

***An Internal SAE is one occurring in a participant that RCH researchers are responsible for, this is independent of where the event occurs.**

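### Section 9.1 leaves seriousness to the investigator's discretion without criteria, so a grave off-list event judged unrelated to the cuff need not reach the ethics committee

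*Protocol*

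**What the plan says.** All of this is in the protocol.

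- **9.1, first rule.** "Adverse event related to the remote preconditioning stimulus will be reported". This covers events attributed to the cuff and sets no threshold of seriousness.
- **9.1, second rule.** "Whether or not an event is a serious adverse event (SAE) is at the discretion of the clinical investigator". No criteria follow.
- **9.1, third rule.** Five events are then fixed: "the following will be considered as severe adverse events and will be reported to the Human Research and Ethics Committee". The duty covers the first 30 days after the operation. The list is death, stroke, mechanical support, permanent disablement and unplanned re-admission.
- **9.2.** SAE data come from the medical notes or, for interstate patients already back at the referring centre, from a telephone interview of the referring doctor. Each SAE is reported with its date, details, management, outcome, expectedness and relatedness.
- **9.3.** SAE forms go to the clinical principal investigators within 24 hours and to the chair of the ethics committee within 72 hours.
- **Appendix (section 16), SAE report form.** All internal SAEs "must be reported to the RCH HREC within 24-72 hours of occurrence". The form explains one of its terms ("An Internal SAE is one occurring in a participant that RCH researchers are responsible for") but not 'serious'. It has separate boxes for expectedness and relatedness.

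**The concern.** Seriousness decides whether an event enters the safety reporting system at all: the form, the two clocks and the ethics committee's view of harm all follow from it. If it has no criteria, two investigators can treat the same event differently and both comply with the protocol. The form already asks for opinion where opinion belongs, on relatedness and expectedness. Seriousness should follow mainly from what happened to the child.

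The change of word adds a second difficulty. Section 9.1 labels its five fixed events 'severe'. Every operational rule after it is written for 'serious' events, and no sentence says that the two words mean the same thing here.

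At stake is whether the ethics committee learns of a life-threatening event after open-heart surgery in a child who took part in the trial.

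**Working it through.** No arithmetic applies: the point concerns the wording of a definition and disputes no stated figure. The check is to take each kind of event through the rules and see whether a report to the ethics committee is compulsory.

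| Kind of event | Rule that applies | Compulsory report? |
| --- | --- | --- |
| One of the five, within 30 days of surgery | 9.1, list | Yes, to the ethics committee. The 9.3 clocks and the form apply only if 'severe' is read as 'serious'. |
| Not one of the five, judged related to the cuff | 9.1, opening sentence | Yes, whatever its seriousness. That sentence names no recipient and no time limit. |
| Not one of the five, judged unrelated, called serious by the investigator | 9.1 discretion, then 9.2, 9.3 and the form | Yes, within the stated times. |
| Not one of the five, judged unrelated, not called serious | None | No. |

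**The last row.** Take a child who has a cardiac arrest in intensive care, is resuscitated without mechanical support, and recovers without stroke or permanent disablement. The event is not death, and it is not a re-admission. Of the five entries, "4. Mechanical support" comes closest, and by construction it does not apply. If the arrest is also judged unrelated to the cuff, only the discretion sentence remains. An investigator who does not call it serious has followed section 9 exactly, and nothing is sent.

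**Does another part of the protocol close the gap?**

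1. *The appendix form.* It demands all internal SAEs but does not define 'serious', so it refers back to 9.1.
2. *The Statement of Compliance.* It commits the study to good clinical practice in general terms. Section 9 neither reproduces nor cites a definition of seriousness from that guidance, and it states a rule of its own.
3. *Outcome data in section 4.4.* Ventilation hours, days in intensive care and in hospital, urine output, urea and creatinine are recorded for every child. A long stay or renal injury would therefore show in the data. Recording an outcome does not trigger a report to the ethics committee.
4. *The sources in 9.2.* Notes and telephone interviews can be searched consistently only against stated criteria. For off-list events there are none.

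None of these makes the report in the last row compulsory.

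**The case against.** The strongest reply is that 9.1 does not contain two competing rules. The natural reading is a mandatory list with freedom to add to it, and 'severe' is a slip for 'serious': the list and the SAE data collection in 9.2 share the same 30-day limit. Harm from the cuff, including the limb compromise that 9.1 names, is reportable in any case. This stands. It confines the problem to off-list events judged unrelated to the cuff. It does not remove it, because freedom to add is also freedom not to add.

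A second reply is that the proposed criteria need judgement too: whether an event threatened life, or lengthened the stay, is not always plain after heart surgery. This stands in part. A stated criterion narrows the judgement and lets someone else check it. The reply is also a good reason not to abolish discretion outright, since discretion is the route for escalating an unusual event that meets no criterion.

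A reader might infer more than the protocol supports:

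- *That the comparison of SAEs between arms rests on opinion.* SAEs are not among the outcomes in section 4.4 or the analyses in 10.3, and the five listed events do not depend on discretion.
- *That the judgement is made unblinded.* Section 6.4 says "Surgeons, perfusionists, anaesthetists will be blinded". It does not state the cardiologist's status, which is not the same as being unblinded. Names are removed from the text, so who decides on seriousness cannot be established.
- *That an interim analysis would have caught the problem.* Section 10.4 schedules none, but an analysis of recorded data cannot show events that were never recorded.
- *That the group size measures the defect.* Confidence limits for an event rate with 20 children per arm would be the same under a perfect definition, and any assumed rate of under-recording would be invented.

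**Conclusion.** The point holds in a limited form. Section 9.1 fixes the classification badly: seriousness has no criteria beyond five events, and those five carry a different label from the one used by the reporting rules. An off-list event judged unrelated to the cuff, even a life-threatening one, can go unreported to the ethics committee with the protocol followed exactly.

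The number of events affected cannot be stated, because the documents give no rates. The conclusion assumes that section 9 and the appendix form contain all the trial's reporting rules and that the general commitment to good clinical practice does not by itself supply the missing definition. If the site applies such a definition in practice, fewer reports would be lost, but the text would still need correcting.

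This is a matter of safety reporting. It does not call any endpoint or stated analysis into question. The change is worth making because it is specific and cheap.

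**What to change.** Amend section 9.1 as follows.

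1. Define a serious adverse event by outcome, with the same criteria in both arms. Include at least life-threatening events and prolonged hospital stay.
2. Keep the five listed events as a minimum. State that the investigator may add to the list but may not narrow it.
3. Use 'serious' throughout, so that the items in 9.2, the clocks in 9.3 and the appendix form plainly apply to every such event.
4. Otherwise confine investigator opinion to relatedness and expectedness, as the form already provides.

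The cost is a short amendment and some additional SAE forms, since events of this kind can be expected after heart surgery in both arms. Nothing in the sample size, the randomisation or the stated analyses has to change.

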# STUDY VISITS AND PROCEDURES SCHEDULE

The subjects are directly studied only during the perioperative period. Blood and myocardial samples are studied upon arrival to the laboratory (mitochondrial studies) or in batches after freezing (proteomic/microscopy studies).

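### Listed serious adverse events are reportable to day 30, but section 9.2 gives same-state children no active check after intensive care, so events outside the trial hospital may be missed

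*Protocol*

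**What the plan says.** Protocol section 9.1 (Definitions) lists five events: death, stroke, permanent disablement, mechanical support and unplanned re-admission. These "will be reported to the Human Research and Ethics Committee if they occur within 30 days of surgery".

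Section 9.2 (Assessment and Documentation of Adverse Events) describes monitoring in theatre and in intensive care, and then states: "Patients will be followed for the period of their intensive care admission which is typically at least 5 days". Section 7 is consistent with a short observation period: "The subjects are directly studied only during the perioperative period".

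The next paragraph of 9.2 names two sources for SAE data:

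- Notes: "SAE data if occurring, will be collected from medical notes for patients cared for at the Royal" Children's Hospital.
- Telephone: "by telephone interview of the referring doctors for interstate patients if they have returned to the referring centre prior to 30 days post-surgery".

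No contact with the family is planned under either route. No date is given for the review of notes or for the call.

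The SAE report form in the Appendix adds a definition: "An Internal SAE is one occurring in a participant that RCH researchers are responsible for, this is independent of where the event occurs".

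**The concern.** The reporting duty and the stated follow-up cover different periods. One listed event, "Unplanned re-admission", cannot happen until the child has left intensive care, whether the term means return to the unit or return to hospital. The sentence that states follow-up therefore stops before that event becomes possible. Everything later depends on the two SAE sources, and these treat children differently according to where they live.

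At stake is the completeness of the protocol's own 30-day safety count in children, which goes to the ethics committee. Followed as written, section 9.2 can under-count it. With 40 children in all, each missed child lowers the 30-day proportion by 1/40 = 2.5 percentage points.

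**Working it through.** The plan states no figure to reproduce. The check sets the passages side by side.

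**Inputs**

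- Reporting window: 30 days after surgery (section 9.1).
- Stated follow-up: the intensive care stay, typically 5 days or more (section 9.2).
- SAE sources: RCH notes, and a call to the referring doctor for returned interstate children (section 9.2).
- Sample: 40 children, 20 per group (sections 4.2 and 5.1.1).
- Share of interstate children: not given.
- Rates of the five events, and the share occurring outside RCH: not given.

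**Step 1. Compare the periods.** At the stated minimum stay, 30 − 5 = 25 days of the window lie after intensive care. A longer stay shortens this: with assumed stays of 10 and 14 days it is 30 − 10 = 20 and 30 − 14 = 16 days. These figures give the part of the window that rests on the two SAE sources. They do not measure events lost.

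**Step 2. Trace each situation through section 9.2.**

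| Where the event happens | Source that applies | Would it be found? |
| --- | --- | --- |
| In intensive care | Bedside follow-up | Yes |
| On an RCH ward, or on re-admission to RCH | RCH notes | Yes, if the notes are reviewed to day 30 |
| Interstate child, returned before day 30 | Call to the referring doctor | Yes, if the call covers the window and the doctor knows of the event |
| Same-state child, at another hospital or at home | RCH notes only | Only if word reaches RCH |

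The last row is the gap. No one outside RCH is asked about these children.

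**Step 3. Try to size the gap.** Let p be the share of interstate children. The number of children without an active check is 40 × (1 − p). Since p is not given, this lies anywhere between 0 (p = 1) and 40 (p = 0). Expected missed events would be that number, multiplied by the event rate after leaving RCH, multiplied by the share of those events that occur elsewhere and never reach the RCH notes. None of these terms is in the protocol, so no count of lost events is offered.

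**Step 4. Consider bias between arms.** Residence is fixed before randomisation and cannot depend on allocation. Under-ascertainment by residence therefore lowers the overall count but is not expected to favour either arm.

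**The case against.** The strongest defence is that the follow-up sentence comes directly after the description of daily limb checks in intensive care and describes bedside observation only. On that reading the next paragraph is the SAE rule. It mentions the 30-day point and gives two ways of covering it. Section 4.4 also records days in hospital, so data collection does not stop at the door of intensive care. SAEs are not a trial outcome, section 10.3 plans no comparison of them between arms, and reports go individually to the ethics committee.

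Most of this stands. A reader might infer from the follow-up sentence that SAE collection ends at intensive care discharge and that all later events elsewhere are lost. The document does not support that: re-admissions to RCH and deaths there should be in its notes, and events in returned interstate children are sought by telephone. A reader might also take the Appendix wording, "this is independent of where the event occurs", as a standard for finding events. It only separates internal from external SAEs for reporting on that form.

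The defence does not supply a source for the same-state child treated or dying outside RCH. It also leaves the follow-up sentence at odds with section 9.1 for anyone who reads it literally.

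**Conclusion.** The point holds in a limited form. Section 9.2 does not reliably deliver the 30-day ascertainment that section 9.1 requires. Listed events in same-state children outside RCH may be missed, and ascertainment for them is less complete than for interstate children who have returned to their referring centre.

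The size cannot be computed from the document. It would be tempting to treat the 25 days after a 5-day stay as the share of follow-up lost, but 5 days is a stated minimum, and the later days are partly covered by notes and calls. It would also be tempting to read this as a threat to the treatment comparison. No such SAE comparison is planned, and residence gives no expected difference between arms.

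The conclusion rests on two readings: that notes means RCH's own notes, and that the call applies only to interstate children, as worded. This is an inexpensive improvement to safety reporting. It does not affect the primary analysis.

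**What to change.** Amend section 9.2 in two places.

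1. Reconcile the follow-up sentence with the 30-day window of section 9.1. If it is meant to describe bedside monitoring only, say so, and state separately that SAE ascertainment runs to day 30 after surgery.
2. Replace the two-route rule with one day-30 SAE check for all 40 children in both arms, wherever they live. One way is a scripted call to the family by existing study staff that asks about each of the five listed events, followed by a records request if any is reported. Extending the existing doctor interview to same-state children would also narrow the gap, but it depends on the doctor having heard of the event.

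The cost is about 40 short calls, a line in the consent form and a protocol amendment. A few families may not be reached. Their number should be reported with the 30-day count, so that it is clear how complete the count is. Treatment and sampling do not change.
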